### Data monitoring

An independent person will be appointed to monitor the study conduct. This monitor will audit both Australia and NZ study sites and the CTRU during the trial to ensure that the study protocol is being adhered to.

At the study sites the monitor will audit every randomized participant's records to ensure their existence, that they meet the inclusion criteria and have provided written and signed informed consent, and that the NRT is been distributed within the limits of the protocol. The monitor will review the study documentation and records held at each site to ensure that (1) documentation is up-to-date [i.e. correct version of protocol and Manual of Procedures] and (2) record keeping meets the requirements specified in the protocol and complies with regulatory requirements. The monitor will visit each site early on during the study (after ten participants have been randomized), at study close-out and once during the course of the trial. At least 10% of paper copies of the CRF's will be checked for consistency with the electronic records by the monitor. 100% of electronic ARI endpoint data will be checked against source data.

The monitor will audit the sites which hold the NRT to check that NRT supply records are in order and that there are sufficient supplies remaining, that the NRT are being stored appropriately and are not being used beyond expiry dates, and that the handling of unused NRT complies with study procedures.

A Data Safety and Monitoring Committee will not be established as the trial does not meet any of the criteria stipulated by Ellenburg et al. (2002) for setting up such a Committee [31].

### Data Analyses

Statistical analyses will be performed by statisticians at the CTRU. The statistical unit at Menzies School of Health Research (Menzies) will play an advisory role. Data from the trial will be entered into an Oracle database at the CTRU, and then extracted into SAS version 9.2 (SAS Institute Inc. Cary NC), and R version 2.8.1 (R Foundations for Statistical Computing) for analysis. Data analyses will be specified *a priori *in a statistical analysis plan prepared by the study statistician (and agreed upon by all members of both the NZ and the Australian Steering Committees). No planned interim analyses will be undertaken of the outcome data. A baseline data paper will be prepared after all baseline data for both countries has been collected. The number of episodes of ARI experienced after the intervention for each group will be analysed on an "intention to treat" basis. Each of the primary and secondary outcome variables will be examined separately. There are no plans to combine outcome variables into composite variables. Data will be analysed for each country separately and combined. All ETS exposure variables will be treated and examined as outcome variables, rather than as co-variates of the primary outcome variable. Intra-rater and inter-country agreement for grading of the primary outcome assessment will be assessed using the Kappa statistic (unweighted), with 95% confidence intervals for the kappa statistic calculated using the method described by Altman [32].

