**Methods/Design:**

This study will be a parallel, randomized, controlled trial. Participants will be Indigenous women and their infants, half of whom will be randomly allocated to an 'intervention' group, who will receive the tobacco control program over three home visits in the first three months of the infant's life and half to a control group receiving 'usual care' (i.e. they will not receive the tobacco control program). Indigenous health workers will deliver the intervention, the goal of which is to reduce or eliminate infant exposure to ETS. Data collection will occur at baseline (shortly after birth) and when the infant is four months and one year of age. The primary outcome is a doctor-diagnosed, documented case of respiratory illness in participating infants.

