## Methods/Design

### Objectives

The primary objective of this study is to determine the efficacy of a family-centred tobacco control program about ETS, to reduce health care presentations for respiratory illness in Indigenous infants in the first year of life. Secondary objectives include assessment of the effect of such a program on a range of measures of infant ETS exposure, including mother/caregiver's self-report of infant exposure to ETS and implementation of smoking restrictions in the home and/or car, infant urinary cotinine, household smoking status, mother/caregiver's smoking cessation and quit attempts. A process evaluation of the family-centred tobacco control program will also be undertaken.

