### Study Design

This study will be a parallel, randomized controlled study with allocation concealed from the study researchers. Participants will be randomly allocated to one of two study arms: the 'intervention' group who will receive the tobacco control program about ETS exposure over three home visits in the first three months of the infant's life, or the control group who will receive 'usual care' (i.e. they will not receive the tobacco control program). IHWs will be trained to deliver the intervention program, the goal of which is to reduce or eliminate exposure of infants to ETS. Data collection will occur at baseline (shortly after birth), and when the infant is four months and one year of age. The primary outcome of interest is the rate of health care presentations for doctor-diagnosed respiratory illness. Figure 1 outlines the flow of participants through the study.

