#### Inclusion Criteria

Infants will be eligible for inclusion if:

• They are aged between 0-5 weeks. (We will review our recruitment rate four months after the trial has commenced. If we find that we are not meeting our enrolment targets, we will consider extending our recruitment to include infants aged 5-10 weeks. This will allow us to approach mothers and their infants at 6-8 weeks when they present at community health clinics for their first immunizations.)

• Their mother/caregiver is Indigenous (defined by maternal self-identification).

• Their mother/caregiver is aged 16 years or over.

• Their mother/caregiver currently smokes or the infant lives in a household where there is at least one other person who smokes (defined as smoking at least weekly).

• Their mother/caregiver plans to reside permanently with the infant in Darwin or Greater Darwin areas of Australia or within the Counties Manukau District Health Board region, Manukau, NZ.

• Their mother/caregiver has given signed written consent to participate in this research study.

• Their mother/caregiver has given signed written consent for study staff to access the infant's health records.

• They are a singleton or the first born in a multiple pregnancy delivery.

• Their mother/caregiver speaks English and/or Māori.

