### Outcome measures

Primary Outcome: *Rate of health provider presentations for new primary episodes of ARI in the first year of life*.

All participating infants will be evaluated at baseline and when the infant is four and 12 months old, for the occurrence of medically attended acute respiratory illnesses (MAARI). These are defined as new onset events, including a change from the child's baseline medical status, referable to the upper and/or lower respiratory tracts. To identify episodes of ARI mothers/caregivers will be asked at baseline, and when the infant is four and 12 months old, whether their child has had any presentation to the clinic or hospital and the names of the clinics attended. Research assistants will collect the source data relevant to the primary outcome measures, so will review the individual child's health provider and hospital clinic records (parental consent will be obtained prior to accessing records). Source documents will be photocopied, de-identified, labeled with the participant registration, and stored with the trial records. Two clinicians at each study centre will review the records and confirm documented respiratory illnesses without knowing the group allocation of the individual children. MAARI events will be evaluated by these clinicians to determine whether they are medically-attended upper respiratory infection (URI), lower respiratory infection (LRI) and/or otitis media infection (based on the definitions in Additional file 1: Table S1). Conflict will be resolved by discussion and consensus between the two clinicians. Intra-rater and inter-country reliability testing will be performed on primary outcome data from 20 participants at each site. Information on antibiotic use for the treatment of medically attended URI, LRI or otitis media events will not be collected.

Major secondary outcomes:

▪ *Rate of hospitalizations for ARI*: same case definition as primary outcome measure.

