### Withdrawal criteria

Participants may be withdrawn from the study if one or more of the following occurs:

• Voluntary withdrawal: A parent or primary caregiver can voluntarily withdraw their infant from the project at any time without having to provide a reason for doing so.

• Failure to meet eligibility criteria: An infant will be withdrawn from the project if their mother/caregiver has previously signed a consent form but they do not meet all the eligibility criteria at the baseline visit (when the infant is five weeks old +/- one week).

• Failure to be located after multiple follow-up home visits

• Death of infant

• Significant illness requiring prolonged hospitalization

• A serious and irreconcilable protocol violation (as determined by the Investigators)

In the event that a study participant dies, their family contact will be asked if they require the information recorded to be disposed of as per other participants at the completion of the study, or whether they wish the information to be returned to the family.

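### The primary outcome is counted over the whole first year in one section and only after the intervention in another, and neither window starts at randomisation

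*Protocol article*

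**What the plan says.** **Outcome measures** names the primary outcome as "Rate of health provider presentations for new primary episodes of ARI in the first year of life". **Objectives** gives the same window: the programme is meant "to reduce health care presentations for respiratory illness in Indigenous infants in the first year of life".

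Ascertainment fits a count from birth. Outcome measures adds: "To identify episodes of ARI mothers/caregivers will be asked at baseline, and when the infant is four and 12 months old", so presentations before the baseline contact are collected too.

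**Data Analyses** gives a different window: "The number of episodes of ARI experienced after the intervention for each group will be analysed on an" intention-to-treat basis. Study Design and Proposed intervention describe the intervention as three home visits spread over about the first three months of age. The control arm does not receive it.

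**Inclusion Criteria** sets age at entry: "They are aged between 0-5 weeks". An extension to 10 weeks will be considered if recruitment falls short, and the randomisation strata already provide for it.

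**Treatment effects** says only that the rate of respiratory illness is compared between the groups. That does not choose between the windows.

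The unit also moves. Study Design counts presentations, Data Analyses counts episodes, and Sample size supports a reduction in new episodes with figures for visits per year.

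**The concern.** Two analysts following different sections of the same article would count different events over different infant-time and report different primary rate ratios. A later analysis plan could choose one window, but it would then contradict a published statement about the primary outcome.

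Each window also has its own weakness:

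- **From birth.** Infants are randomised some weeks after birth. Episodes before that date are unaffected by allocation, so they pull the rate ratio towards 1.
- **After the intervention.** Read plainly, this omits episodes between randomisation and about three months of age. Control infants have no programme and therefore no programme end date, and the article gives no substitute. That sits badly with the intention-to-treat label in the same sentence, unless one age start is used in both arms.

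**Working it through.** **Inputs.** From Sample size: 190 infants in total, 3 against 2.25 visits per year, Poisson variance, 5% significance, 90% power; for both countries combined, 380 infants and an 18% reduction. From the abstract: half to each arm, so 95 (or 190) per arm. From Treatment effects: two-tailed tests. From Inclusion Criteria: entry at 0-5 weeks, possibly to 10.

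**Assumptions.** The event rate is constant at 3 per year, and the full reduction acts from randomisation onwards. The article does not date randomisation beyond the age limits, so I show entry at 2.5, 5 and 10 weeks.

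**Formula.** Power = Φ[(λ1 − λ2) / √((λ1 + λ2)/n) − 1.96], where λ1 and λ2 are expected episodes per control and intervention infant and n is the number per arm.

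**The plan's own figure.** 0.75 / √(5.25/95) = 3.19, and Φ(3.19 − 1.96) = 89.1%. For 3 against 2.46 with 190 per arm, power is 89.0%. Both are close to the stated 90%, but only if the full effect acts over all 12 months.

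**Count from birth.** With entry at w weeks, the share of control events before randomisation is f = w/52: 4.8%, 9.6% and 19.2%. The apparent reduction is 25% × (1 − f): 23.8%, 22.6% and 20.2%. Expected episodes are 3 in control and 3 × [f + 0.75(1 − f)] in intervention. At 5 weeks this is 3 against 2.322, giving 0.678 / √(5.322/95) = 2.86 and power 81.7%.

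**Count from randomisation.** Expected episodes are 3(1 − f) and 2.25(1 − f). At 5 weeks this is 2.71 against 2.03, giving 0.678 / √(4.745/95) = 3.03 and power 85.8%.

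| Entry age | Apparent reduction, from birth | Power, from birth | Power, from randomisation | Difference (points) |
|---|---|---|---|---|
| 2.5 weeks | 23.8% | 85.7% | 87.6% | about 2 |
| 5 weeks | 22.6% | 81.7% | 85.8% | about 4 |
| 10 weeks | 20.2% | 72.0% | 81.8% | about 10 |

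The combined sample (190 per arm, 18% reduction) gives almost the same powers: 85.7%, 81.7% and 72.2% from birth, against 87.5%, 85.7% and 81.7% from randomisation.

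**Count after three months.** Expected episodes are 3 × 9/12 = 2.25 and 2.25 × 0.75 = 1.6875. Then 0.5625 / √(3.9375/95) = 2.76 and power is 78.9%. The post-randomisation time dropped is (13 − w)/(52 − w): 25%, 17% and 7% for entry at 0, 5 and 10 weeks.

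**The case against.** The best defence is that most of the article points one way. Hypothesis, Objectives, Outcome measures and the yearly rates in Sample size all imply the first year, so the Data Analyses phrase may be loose wording for after allocation. That is possible, but nothing in the article says so. Even that reading would conflict with a count from birth.

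A reader might infer that the randomised comparison is broken. The article does not support this. It states no arm-specific start date. The programme is tied to infant age, and all infants are assessed at four months, so a common age start is available. Analysing a fixed-age window by allocated arm does not in itself breach intention to treat. Events before randomisation are balanced in expectation, so counting them costs efficiency and clarity, not validity.

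A reader might also set the 82% and 72% against the planned 89% and blame the window for losses of 7 and 17 points. That is the wrong comparator, because counting from randomisation also shortens follow-up. The recoverable part is the last column of the table. The 10-week row further assumes that the extension is used and that every infant enters at its upper limit.

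The power argument does not always favour randomisation. If the effect began only at three months, a count from randomisation with entry at 5 weeks would expect 2.71 against 2.71 − 0.5625 = 2.15 episodes. Its power would be about 70%, below the 79% for the after-three-months count. The reason to start at randomisation is therefore a defined, common, allocation-based start, with power secondary.

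Two further differences do not strengthen the point. The abstract's looser description of the outcome is shorthand. The two descriptions of baseline timing differ in precision and are not a clear contradiction.

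**Conclusion.** The point holds as an inconsistency in the definition of the primary variable. The current text gives two windows for it, and neither begins at randomisation. Taken literally, one yields a diluted count and the other a truncated count with no stated start in controls.

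The size is moderate. Under a constant rate and an immediate full effect, counting from birth costs about 2 to 4 power points for entry at 2.5 to 5 weeks, and about 10 if all infants entered at 10 weeks. Dilution would be smaller if respiratory illness is rarer in the first weeks of life. The need for one window does not rest on these power figures.

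**What to change.** State one primary window in Objectives, Outcome measures and Data Analyses: adjudicated new ARI episodes from randomisation to 12 months of age, in both arms, analysed as a rate per infant-time. In Data Analyses, make the count run from randomisation instead of from the intervention. If a later start is of interest, keep it only as a supportive analysis with one fixed age in both arms. Use new episodes as the unit throughout, including in Sample size.

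The cost is wording only, since the clinic and hospital records needed to date the events are already to be collected. There is one small downside: infant-time is shorter than the full year assumed in Sample size, so the stated 90% power becomes somewhat less favourable (about 88% to 86% for entry at 2.5 to 5 weeks on the assumptions above).

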#### Baseline characteristics

All known potential confounders will be measured at baseline, including mother/caregiver's smoking status (and stage of change), education level, marital status, breastfeeding status, smoking status of partner and other household members, crowding, and exposure of infant to other sources of environmental smoke (e.g. cannabis, open fires). Thus, comparisons of the intervention and control groups will be performed both unadjusted and adjusted for these known confounders. This second adjusted analysis will control for any maldistribution after randomisation of the confounders between the two groups.

#### Treatment effects

Analysis of the primary outcome will involve comparing the rate of respiratory illness between the two groups. Simple unadjusted rates, relative risks and 95% confidence intervals will be obtained in the first instance, with subsequent multiple regression analysis adjusting for other variables. Two forms of regression analysis will be considered for the primary outcome: poisson regression analysis and negative binomial if there is evidence of overdispersion or underdispersion. Analysis of secondary outcomes will be conducted using standard statistical procedures applicable to categorical or continuous data. A per-protocol analysis will also be performed in order to check the robustness of the results. All tests of significance will be two-tailed.

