### Randomisation: allocation concealment and sequence generation

Participants will be randomized by computer with stratification using permuted blocks by country (Australia, NZ) and infant age (0-5 weeks, >5-10 weeks). This will ensure a balance in these key prognostic indicators between the intervention and control groups. All participants (i.e. the infants) will be assigned a unique registration number allocated by a central computer following the submission of their details on a web-based form.

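### The analysis text does not carry the stratification factors into the combined model; if country rates differ and dispersion is estimated, the reported standard error is too large and the test conservative

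*Protocol article*

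**What the plan says.** The section on randomisation states: "Participants will be randomized by computer with stratification using permuted blocks by country (Australia, NZ) and infant age (0-5 weeks, >5-10 weeks". It gives the reason in the next sentence: "This will ensure a balance in these key prognostic indicators between the intervention and control groups".

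Treatment effects sets the order of analysis for the primary outcome: "Simple unadjusted rates, relative risks and 95% confidence intervals will be obtained in the first instance", "with subsequent multiple regression analysis adjusting for other variables". The model is Poisson, or negative binomial if the data show over- or underdispersion.

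Baseline characteristics describes the adjustment variables: "All known potential confounders will be measured at baseline, including mother/caregiver's smoking status (and stage of change), education level, marital status, breastfeeding status", followed by household smoking, crowding and other smoke sources. It adds that "comparisons of the intervention and control groups will be performed both unadjusted and adjusted for these known confounders". The stated purpose of adjusting is to deal with imbalance that arises after randomisation. The list is open, since it is introduced by the word including, but neither country nor infant age is on it.

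Data Analyses provides for an analysis of each country separately and of both combined. It also says: "All ETS exposure variables will be treated and examined as outcome variables, rather than as co-variates of the primary outcome variable". Sample size relies on the combined analysis (380 infants) for 90% power to detect an 18% reduction.

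**The concern.** The design treats country and infant age as prognostic, while the analysis text leaves them out of both the first comparison and the named covariates. The stated reason for adjusting makes this more than an unfinished list. If covariates are chosen to correct chance imbalance, factors balanced by design are the first to be dropped. Yet for those factors the usual unadjusted standard error does not credit the balance that stratification achieved. In a count model that estimates dispersion, a difference in rates between countries then appears as extra spread, and the interval for the treatment effect becomes too wide.

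The combined analysis is where this matters. The protocol concedes that the 25% effect used to size each country may be optimistic and turns to the combined data for the smaller effect.

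A second, smaller point is wording. The rule that smoke-exposure variables are outcomes and not covariates has no time limit, while Baseline characteristics lists maternal and household smoking status as adjustment variables. Objectives names household smoking status among the measures of infant exposure.

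**Working it through.** **Inputs from the protocol (Sample size, Treatment effects).** Combined N = 380, taken as 190 per arm and 95 per arm per country; control mean 3 visits; rate ratio 0.82, so |ln 0.82| = 0.1985; two-sided 5%; Poisson variance.

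**Assumed, because the protocol gives no country-specific rates.** Control means of 2 and 4 in the two countries (average 3), with other ratios below. Within-country variance = mean + k × mean², with k = 0 or 0.35.

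**Step 1: the protocol's own figures.**
- Combined: SE = √[1/(190 × 3) + 1/(190 × 2.46)] = √0.00389 = 0.0624. Power = Φ(0.1985/0.0624 − 1.96) = 88.9%, against 90% stated.
- One country: SE = √[1/(95 × 3) + 1/(95 × 2.25)] = 0.0905. Power = Φ(0.2877/0.0905 − 1.96) = 88.9%, against 90% stated.

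Both agree with the protocol to within about one percentage point.

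**Step 2: reported SE without country, k = 0, means 2 and 4.** Each arm's variance is the average within-country variance plus the between-country part.
- Control: (3 + 1)/(190 × 3²) = 0.00234.
- Intervention (means 1.64 and 3.28): (2.46 + 0.6724)/(190 × 2.46²) = 0.00272.
- Reported SE = √0.00506 = 0.0712.

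**Step 3: true SE without country.** Stratified allocation puts equal numbers from each country in each arm, so the between-country part cancels. The variance is 3/(190 × 3²) + 2.46/(190 × 2.46²) = 0.00389, giving SE = 0.0624, the same as with country in the model.

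**Step 4: power and type I error, k = 0.**
- Without country: Φ[(0.1985 − 1.96 × 0.0712)/0.0624] = 83%.
- With country: 88.9%.
- Under no effect, the reported SE is √(2 × 4/1710) = 0.0684 and the true SE √(2 × 3/1710) = 0.0592, where 1710 = 190 × 3². The effective critical value is 1.96 × 0.0684/0.0592 = 2.26, a two-sided error of about 2.4%.

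**Step 5: the same with k = 0.35.**
- Control: within-country variance (3.4 + 9.6)/2 = 6.5, plus 1 between. Intervention: (2.581 + 7.045)/2 = 4.813, plus 0.672.
- Reported SE = √(7.5/1710 + 5.486/1149.8) = 0.0957, where 1149.8 = 190 × 2.46². True SE = √(6.5/1710 + 4.813/1149.8) = 0.0894.
- With country (inverse-variance pool of the two country estimates): √0.00780 = 0.0883.
- Power: Φ[(0.1985 − 1.96 × 0.0957)/0.0894] = 55% without; Φ(0.1985/0.0883 − 1.96) = 61% with.

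**Step 6: simulation** (stratified 1:1 allocation, N = 380, means 2 and 4, Poisson fit with standard error scaled for dispersion).

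| | Reported SE, without / with country | Power, without / with | Type I error, without |
|---|---|---|---|
| k = 0 | 0.071 / 0.063 | 83% / 89% | 2.6% |
| k = 0.35 | 0.096 / 0.087 | 56% / 62% | 3.6% |

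The point estimate and its empirical SE were the same with and without country. A negative binomial fit at k = 0.35 gave empirical SEs of 0.0902 and 0.0899.

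**Step 7: range over the assumed country difference, k = 0, formula of Step 4.**
- Equal rates: reported SE 0.0624; no loss.
- 2.4 and 3.6: reported SE 0.0657; power Φ[(0.1985 − 1.96 × 0.0657)/0.0624] = 87% against 89%.
- 2 and 4: 83% against 89%.
- 1.5 and 4.5: reported SE 0.0808; power Φ[(0.1985 − 1.96 × 0.0808)/0.0624] = 74% against 89%.

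**Step 8: plain Poisson.** Its reported SE depends only on total counts, so it stays at 0.0624 with or without country.

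**The case against.** The strongest reply is that this belongs to the statistical analysis plan, to which the article defers and which is not shown. The covariate list is open, Treatment effects speaks only of other variables, and nothing excludes country or age. That stands in part: the plan may already include both. But the article goes beyond deferring. It fixes an order, names covariates and gives a rationale, and a plan faithful to that rationale would leave balanced strata out.

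It is also fair that no sentence makes the unadjusted result primary; being first in order is not the same thing. The separate country analyses already condition on country, so only the combined one is affected.

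A reader might infer that ignoring the strata makes the treatment estimate itself less precise, by 15% to 23% of its variance under the assumed means of 2 and 4. Step 3 shows otherwise: stratified allocation has already secured the gain. At k = 0 the true variance is identical, and at k = 0.35 it falls from 0.00799 to 0.00780, about 2%. Only the reported standard error is wrong.

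A reader might also see opposite instructions on smoking covariates. The text does not force that reading. The exposure rule concerns variables examined as outcomes, and Baseline characteristics concerns values measured at baseline. The wording is ambiguous but can be reconciled.

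**Conclusion.** The mismatch between design and analysis text is real and worth correcting, but its cost is conditional. It arises only in the combined analysis, only if country rates differ, and only under a model that estimates dispersion. The last condition is plausible: a country difference left out of the model itself looks like overdispersion and so favours the negative binomial option.

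With assumed means of 2 and 4, the loss is about six percentage points of power (83% against 89% at k = 0; about 56% against 62% at k = 0.35), and the type I error falls below the nominal 5%. The low power at k = 0.35 comes mainly from the overdispersion itself, which a country term does not remove. Under plain Poisson or with equal country rates there is no loss. The error is in the conservative direction, so it does not threaten the validity of a positive finding.

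No figure can be put on infant age. The older stratum exists only if recruitment is extended, and the protocol gives no age-specific rates.

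**What to change.** State that the primary result of the combined analysis is the rate ratio from a model that includes country, and infant-age stratum if both age strata are enrolled. Present the unadjusted rates and relative risk as descriptive, and the model with the further baseline covariates as secondary.

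Add a clause to Data Analyses saying that the rule on smoke-exposure variables applies to measures taken after randomisation, so that the baseline smoking covariates listed under Baseline characteristics are plainly allowed.

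Both are changes of wording. The stratification factors are recorded at randomisation, and no extra data or participants are needed.

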### Sample size

A total sample size of 190 provides 90% power (5% significance) to detect a 25% reduction of new episodes of respiratory illness (primary outcome) in the intervention group compared to the control group. This is based on a conservative estimate of an average of 3 health provider visits per year in the control group, compared to an average of 2.25 visits in the intervention group (assuming a Poisson distribution where the mean equals the variance). There are few published data on the community burden of ARIs in Northern Territory Indigenous children or NZ Māori children. In a recent study of disease burden and clinic attendances for young Indigenous children in two remote Northern Territory communities, the median number of presentations for upper respiratory illness in the first year of life was 7.5 (interquartile range 4-11) and for lower respiratory illness, 2.5 (interquartile range 1-5) [28]. The overall number of episodes of respiratory illness is likely to be less in an urban setting compared to that in the remote contexts [29]. Thus, it is estimated that an average of 3 visits per year be undertaken in the control group for the sample size calculation above. A maximum of 10% loss to follow-up is expected, as there are multiple contact points throughout the study for both groups and because the primary outcome (rate of respiratory infections) even in children who leave the study region before 12 months of age can be measured. Thus, 210 children in each country will be recruited. Given that there are limited data to base the likely effect size on, it is possible that the effect size chosen may be optimistic. By combining data from NZ and Australia the sample size is increased to 380 participants (420 if loss to follow-up is factored in), which will provide 90% power (at 5% significance level) to detect an 18% reduction in new episodes of ARI in the intervention group compared to the control group.

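### The negative binomial is named as the remedy for underdispersion, which it cannot model; one count model with a variance valid in both directions should replace the dispersion check

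*Protocol article*

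**What the plan says.** The primary outcome (Outcome measures) is "Rate of health provider presentations for new primary episodes of ARI in the first year of life", so each infant contributes a count over a period of follow-up.

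Under Treatment effects the analysis has two steps. First: "Simple unadjusted rates, relative risks and 95% confidence intervals will be obtained in the first instance". No variance method is given for these intervals. Adjusted regression follows, and two forms are to be considered for the primary outcome: "poisson regression analysis and negative binomial if there is evidence of overdispersion or underdispersion". In addition, "All tests of significance will be two-tailed".

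The Sample size section takes "an average of 3 health provider visits per year in the control group, compared to an average of 2.25 visits in the intervention group". Its calculation sets the variance equal to the mean, as for a Poisson count. The same section cites first-year counts from two remote communities: upper respiratory presentations with median 7.5 and interquartile range 4 to 11, and "for lower respiratory illness, 2.5 (interquartile range 1-5").

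Data Analyses promises a statistical analysis plan written in advance (not shown here). Blinding states that the trial statisticians will not know group assignment.

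**The concern.** Two features of the regression rule look wrong as stated.

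1. It sends both departures from Poisson to the same model. The negative binomial can represent a variance above the mean, not one below it. For underdispersion the stated remedy does nothing.
2. It settles the form of the primary model by inspecting the dispersion of the outcome, although the protocol's own cited data suggest which way the dispersion will go.

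A further question is how far the rule reaches. It governs the regression step, whereas the unadjusted rates and intervals come before it. If those intervals assumed that variance equals mean while counts were overdispersed, the first comparison reported would look more precise than it is. What is at stake is whether the interval around the primary rate ratio has its nominal coverage.

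**Working it through.** **Inputs.** From Sample size: means 3 and 2.25, two-sided 5%, 90% power, 190 infants per country (95 per arm), 380 combined (190 per arm), and the two interquartile ranges. Assumptions: the values of k below, and a 5% Pearson chi-square test in each tail as the dispersion check.

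**The plan's own figure.** With variance equal to mean, the number per arm is (1.96 + 1.2816)² × (3 + 2.25) / 0.75² = 98.1, or 198 in total. At 190, power is Φ(0.75 / √(5.25/95) − 1.96) = Φ(1.23) = 0.89. The stated 190 is thus reproduced to within about one point of power, and the calculation does rest on Poisson variance.

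**Underdispersion.** The negative binomial variance is μ + kμ² with k ≥ 0. Its minimum is μ, at k = 0, where it is Poisson. If the true variance-to-mean ratio is φ and the analysis uses variance μ, type I error is 2[1 − Φ(1.96/√φ)] and the interval is 1/√φ times the correct width.

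- φ = 0.75: 1.96/0.866 = 2.26, error 0.024, interval 1.15 times too wide.
- φ = 0.50: 1.96/0.707 = 2.77, error 0.006, interval 1.41 times too wide.

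Simulation under no effect (mean 3, 3,000 runs per setting, Monte Carlo standard error about 0.004) agrees. With 95 per arm, Poisson and negative binomial both give 0.023 and 0.006; scaled Poisson gives 0.049 and 0.053.

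**Dispersion implied by the cited ranges.** By normal approximation, SD = IQR/1.349.

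- Upper respiratory: 7/1.349 = 5.19, variance 26.9, mean about 7.5, ratio 3.6, k = (26.9 − 7.5)/7.5² = 0.35.
- Lower respiratory: 4/1.349 = 2.97, variance 8.8, mean about (1 + 2.5 + 5)/3 = 2.83, ratio 3.1, k = (8.8 − 2.83)/2.83² = 0.74.

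A negative binomial fit to the quartiles gives k of 0.31 and 0.68. A Poisson count with mean 7.5 would have quartiles 6 and 9, not 4 and 11.

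**The two-step rule under overdispersion.** Simulated type I error, mean 3, no effect, 95 per arm:

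| k | Poisson kept | Two-step rule | Negative binomial always | Share switched |
|---|---|---|---|---|
| 0.05 | 0.066 | 0.055 | 0.049 | 39% |
| 0.10 | 0.088 | 0.056 | 0.053 | 81% |
| 0.20 | 0.121 | 0.049 | 0.049 | 99.7% |
| 0.33 | 0.157 | 0.047 | 0.047 | 100% |
| 0.50 | 0.215 | 0.056 | 0.056 | 100% |

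With 190 per arm the two-step rule gives 0.049 to 0.057. Fixing the negative binomial in advance changes type I error by at most about 0.6 points.

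**If the unadjusted intervals used Poisson variance.** At mean 3, φ = 1 + 3k.

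- k = 0.33: φ = 1.99, interval 1/√1.99 = 0.71 of the correct width, simulated error 0.157 (formula 0.165).
- k = 0.5: φ = 2.5, interval 0.63 of the correct width, simulated error 0.215.

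**The case against.** A reader might infer something stronger: that starting from Poisson gives the primary result intervals that are too narrow, with a type I error of 16 to 21% or more. The article does not support this. The sentence that names Poisson also moves to the negative binomial when overdispersion is seen, and at k of 0.2 or more the simulated rule does so in practically every trial. The high error rates describe a regression that always keeps Poisson, which is not the plan.

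A reader might also infer that the analyst could pick between two p-values. The dispersion test and its threshold belong in the analysis plan that Data Analyses promises, and the statisticians are to be blinded to group. A dispersion check made blind is not a choice between treatment results.

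The unadjusted intervals could use between-infant variance or a bootstrap, so calling them too narrow is conditional. The cited ranges come from remote communities, and Sample size itself expects fewer episodes in urban settings. Finally, if counts are overdispersed the underdispersion branch is never reached, and if it were, the error would be conservative.

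All of this stands, and it makes the point a modest one. It does not rescue the remedy for underdispersion, which is a wrong statement about the primary model rather than a detail left for later. Nor does it give a reason to keep a dispersion check that a single suitable model makes unnecessary.

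**Conclusion.** The rule is wrong as written in one definite respect: the negative binomial cannot correct underdispersion. In that case intervals stay about 1.15 times (variance-to-mean ratio 0.75) to 1.41 times (0.50) too wide, with type I error near 2% and below 1%. That result follows from the variance formula.

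The dispersion check is unnecessary rather than damaging, since type I error stays near 5% under the assumed 5% test. Intervals that are too narrow remain a possibility only for the first-step unadjusted comparison, and only if it uses Poisson variance. The 16 to 21% then depends on k of 0.33 to 0.5 applying at a mean of 3 in these urban populations. That range is an assumption: its lower end matches the cited upper respiratory counts, and its upper end lies below the lower respiratory value.

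**What to change.** Under Treatment effects:

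- Delete underdispersion as a trigger for the negative binomial.
- Pre-specify one primary log-link count model with a log person-time offset and a variance that is valid in both directions: Poisson or negative binomial with a robust (sandwich) variance, or scaled Poisson. A negative binomial with model-based variance alone would not meet this, because it fails under underdispersion.
- Use that model for both the unadjusted and the adjusted comparison, so that the first-step intervals are covered too, and call the result a rate ratio rather than a relative risk.

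This is a change of wording before analysis, with no effect on data collection. In the simulations scaled Poisson held type I error at 0.047 to 0.056 across every setting, over-, under- and exactly Poisson-dispersed. The downside is a negligible loss of efficiency if counts are exactly Poisson.
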